## 3.2 Overall study design

A mixed-methods design will be used, based upon the Reach Effectiveness Adoption Implementation Maintenance (RE-AIM) framework (see <http://www.re-aim.hnfe.vt.edu/>). RE-AIM is a widely used framework to evaluate the impact of public health interventions by assessing five key domains: reach, effectiveness, adoption, implementation, and maintenance. The research methods will include a routine cohort data design, secondary analysis of pre-existing cross-sectional survey data, clinical audit, self-administered medication adherence survey, qualitative research and use of routine service data. This mixed methods approach is being used in order to address the study objectives within the overarching RE-AIM framework. Data from the quantitative and qualitative portions of this study will be triangulated and presented in a descriptive report. Further details on the study indicators and data sources, analysis and management are described in detail under each methodology section below and are summarised in Table 2 and Figure 1.

## 3.3 Study population

The study population for this evaluation consists of four groups:

1. The broader study population, which was included in the pre-existing, completed cross-sectional household survey, consisted of UNHCR-registered and unregistered Syrian refugees living outside of official camp settings within Irbid governorate.

2. Patients enrolled in MSF’s NCD clinics:

This refers to non-camp-dwelling Syrian refugees and vulnerable Jordanians who have been enrolled in MSF’s vertical NCD clinics in Irbid, Jordan, since patient registration was introduced in December 2014. To date (November 2016), 4672 NCD-related patients (aged 1 to 94 years) have been registered in the two clinics. Inclusion criteria are (1) Socio-demographic [Syrian refugee, refugee from another origin or vulnerable Jordanian (defined as patients who were identified as vulnerable according to the Ministry of Social Development National Aid Fund list)] and (2) Medical [confirmed CVD (including angina pectoris, myocardial infarction, ischaemic stroke, peripheral vascular disease), CVD risk factors (HTN), COPD, Asthma and/or DM]. Patients must fulfil both criteria.

The routine cohort data analysis, including the clinical audit, will include data from all enrolled patients aged six years and above (using files of patients admitted from January 2015 through to December 2016); qualitative data gathered through focus group discussions (FGDs) and semi-structured interviews (SSIs), and data from the adherence survey will be collected from a sample of adult patients aged 18 or older.

3. Clinic staff:

Semi-structured interviews will also take place with current and former healthcare workers and MSF management staff who provide(d), supervised or supported MSF NCD services in Irbid, Jordan.

4. Key Stakeholders:

Informal interviews will take place with key stakeholders, including members of the Jordanian Ministry of Health; Irbid District Health Office; clinical manager of the Ibn Sena MoH clinic where MSF‘s clinic is co-located; and Syrian refugee community leaders.

The eligibility criteria, recruitment and sampling methods are described further under each methodology’s sub-section below.

## 3.4 Cohort study method

The cohort design seeks to describe the patient cohort and explore clinical and quality of care outcomes of the NCD programme by analysing routine clinical data and performing a clinical audit of patient files from the two clinics. This evaluation does not seek to formally evaluate programme effectiveness since this programme has evolved over time and there is no single intervention that can be evaluated nor do we have a comparator group. Thus, we have chosen to evaluate to what extent the programme is: a) consistently implementing the evidence-based clinical guideline which incorporates interventions known to reduce mortality and morbidity e.g. appropriate statin prescribing, and b) achieving evidence-based targets for disease control e.g. blood pressure control. The cohort study will also include descriptive costing analysis.

### 3.4.1 Cohort study area and study population

The study location will be the two MSF-OCA supported clinics in Irbid city, northern Jordan. The first clinic was opened in December 2014 within an MoH primary care facility in Ibn-Sena and the second, opened in April 2015, works alongside a private organization, Arab Medical Relief (AMR), in their facility at Ibn-Rushd.

To date (November 2016), 4672 NCD-related patients (aged 1 to 94 years) have been registered in the two clinics, since patient registration was introduced in December 2014. Inclusion criteria are (1) Socio-demographic [Syrian refugee, refugee from another origin or vulnerable Jordanian (defined as patients who were identified as vulnerable according to the Ministry of Social Development National Aid Fund list) and (2) Medical [confirmed CVD (including angina pectoris, myocardial infarction, ischaemic stroke, peripheral vascular disease), CVD risk factors (HTN), COPD, Asthma and/or DM Type I or II]. Patients must fulfil both criteria. All NCD patients aged six years and older with at least two recorded visits (to enable evaluation of outcomes) will be included in the study cohort. This includes any new patients presenting with a new or existing diagnosis of a target NCD.

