**Methods:**

*Design*: A mixed-methods design will be used, based upon the RE-AIM framework (see <http://www.re-aim.hnfe.vt.edu/>). Objective 1 (Reach) will refer to a pre-existing dataset from a random cross-sectional population-level household survey previously conducted by MSF for separate purposes; routine cohort data from two MSF clinics in Irbid; and qualitative data from focus groups, semi-structured and key informant interviews. Objective 2 (Effectiveness) will use a cohort study design of chronic disease patients at the MSF-run clinics in Irbid. It will use routine clinic data to explore trends in clinical outcomes and other quality of care indicators, which occurred during MSF’s implementation of this NCD care model in Irbid. It will also include descriptive analysis of total and unit programmatic costs. Objective 3 (Adoption/acceptance) will use qualitative data to explore issues around adoption and acceptance of the model components through participant observation, focus group discussions and semi-structured interviews with patients, staff and key stakeholders. A small exploratory study to develop and test a short survey of self-reported medication adherence and beliefs will also be undertaken. Objective 4 (Implementation) will use routine cohort data, clinical audit, participant observation, routine costing data and qualitative data (as described above). Objective 5 (Maintenance) uses routine cohort data, qualitative data (as described above) and data on medical supplies, costs and staff time estimates.

*Study participants:* The pre-existing cross-sectional health service access survey included Syrian refugees households living outside of camp settings in Irbid governorate, selected using a two-stage cluster design. For the routine cohort data, all patients six years and older with confirmed NCDs attending the two MSF clinics in Irbid more than once, will be included (using patient records from January 2015 to December 2016). For the qualitative research, respondents will be purposively selected patients and/or health workers, past and present, from the two MSF clinics in Irbid. Key stakeholder interviews will include staff from MSF and other NGOs, Jordanian MoH staff and community leaders. For the medication adherence survey, a random sample of 300 consenting service users attending the MSF clinic will be selected.

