| “Effectiveness”/ Quality of Care  What are the trends in clinical outcomes and quality indicators of the programme?  What are the perceived benefits/unintended consequences from a patient and provider perspective? | Clinical Outcomes | No./% patients with hypertension that have a most recent BP <= 140/90 6 and 12 months post enrolment and trend from baseline  Number / % of patients with diabetes that have a most recent BP <= 140/90 6 and 12 months post enrolment and trend from baseline  Number / % of patients with diabetes with last HbA1c < 8.0 %/ 7.0 % 6 and 12 months post enrolment and trend from baseline  Number/% with a reduction of >= 0.5 mmol/L in cholesterol level from baseline 6 and 12 months from enrolment  Number/% of patients with asthma / COPD free from exacerbations/ admissions in the previous 6 months  Number / % of patients who report decreased/quitting smoking within reporting period  Number / % of patients who report increased levels of exercise from baseline during reporting period  Trend recommended referrals to another facility for acute complications/specialist care, as a proportion of active cohort | Routine facility cohort data  Costing data (for incremental costing analysis)  2 Focus group with patients  Semi-structured interviews with approximately 12 clinic staff and 16 patients |
|  | Quality Indicators | Proportion of recommended referrals to other services that are appropriate as per guideline  Number/ % of active patients with CVD prescribed a statin during reporting period  Number/ % of patients with CVD prescribed aspirin during reporting period  Number/ % of patients with CVD prescribed at least one anti-hypertensive during reporting period  Number/% of patients with COPD/asthma with inhaler technique check documented  Number/ % of times when appropriate clinical action taken based on clinical or laboratory findings according to guideline (see Annexe 2d for detail)  Trend in defaulters as a proportion of active cohort during reporting period  Description of cohort deaths (patient characteristics) | Clinical audit  Participant observation  Routine health facility cohort data |
|  | Perceived Effectiveness | Patient and providers perspectives on effectiveness of programme components (clinical review, medications, HE, HLO, MHPSS, HV) | Key informant interviews  2 Focus groups with patients  Semi-structured interviews with 12 MSF/clinic staff and 16 patients |

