| Maintenance  What are the challenges and facilitators for patients to remain in the programme?  What are the costs involved in maintaining the programme?  What are the programmatic challenges and adaptations made to maintain the programme? | Individual Level | Number/% of patients active 6 months post enrolment in reporting period  Numbers of medications and daily pill count at last consultation during reported period  Self-reported medication adherence rates and medication beliefs  Qualitative measure of individual-level maintenance:  Key challenges in maintaining medical treatment (including medication concordance)  Key challenges in altering lifestyle (diet, exercise, smoking)  Key mental health/ psychosocial challenges  Types of support available and strengths and challenges of the support (health education, MHPSS, HLO, family and community support) | Routine facility cohort data  Clinical Audit  Key informant interviews  2 Focus groups with patients  Semi-structured interviews with 12 MSF/clinic staff and 16 patients  Medicine/supply/staff costs  Staff time estimates  Self-report medication adherence questionnaire |
|  | Organisational Level | Measures of cost of maintenance  Institutionalisation of the programme/modifications made for maintenance  Alignment with organizational mission |  |

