### 3.4.2 Cohort study main outcome measures

The principal **clinical outcome measures** for patients in the cohort are:

DM: HbA1c < 7 or 8%; proportion of patients meeting individualised target at last visit within the reporting period and trend from baseline

Hypertension: BP < 140/90 mmHg: proportion of patients at target at last visit within the reporting period and trend from baseline

Cardiovascular disease: change in total cholesterol level from baseline

Asthma / COPD: Free from exacerbations / admissions in last six months

The principal **quality of care outcome measures** are the following:

Number/ % of active patients with CVD prescribed a statin during reporting period

Number/ % of patients with CVD prescribed aspirin during reporting period

Number/ % of patients with CVD prescribed at least one anti-hypertensive during reporting period

Number/% of patients with COPD/asthma with inhaler technique check documented

Number/ % of times when appropriate clinical action taken based on clinical or laboratory findings according to guideline (see Annexe 2e for detail)

Description of trends and patient characteristics in programme defaulters and deaths

Proportion of recommended referrals to other services that are appropriate as per guideline

Death is defined as confirmed death reported by family or community member. A defaulter is defined as a patient who has not attended any NCD clinic appointments within the last 90 days, is not known to have died or moved out of the area, and has not been successfully contacted by phone on two occasions by the clinic registrar. The definition was changed in October 2016 to reflect the newly extended appointment interval for stable patients to: two consecutive missed appointments; not known to have died, moved out of the area, or become immobile and ineligible for home care; and has not been successfully contacted by phone on two occasions by the clinic registrar.

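### The two-visit entry rule removes patients lost after their first visit, so 6-month retention is overstated and the account of default and death is incomplete

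*Protocol*

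**What the plan says.** Protocol section 3.4.1 limits the cohort to patients "aged six years and older with at least two recorded visits (to enable evaluation of outcomes) will be included in the study cohort". The executive summary agrees: confirmed NCD patients "attending the two MSF clinics in Irbid more than once, will be included".

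Section 3.3 is looser. It says the routine cohort analysis "will include data from all enrolled patients aged six years and above", with no condition on visits, but it closes by stating that "The eligibility criteria, recruitment and sampling methods are described further under each methodology’s sub-section below".

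Three sets of measures then depend on who is in the cohort:

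- Section 3.4.2 lists among the principal quality-of-care outcomes "Description of trends and patient characteristics in programme defaulters and deaths".
- Table 2, Quality Indicators, adds "Trend in defaulters as a proportion of active cohort during reporting period" and "Description of cohort deaths (patient characteristics".
- Table 2, Maintenance, Individual Level, lists "Number/% of patients active 6 months post enrolment in reporting period", with routine facility cohort data among its sources.

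No separate population is named for any of these, and section 6 (Limitations) does not mention the exclusion of single-visit patients.

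**The concern.** Returning for a second visit is itself a form of retention. A patient who attends once and then stops coming, or dies, is left out because of the event that these indicators are meant to capture. Nobody in the cohort can be lost between visit 1 and visit 2.

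This matters because section 2 describes the model as aimed at limiting interruption of treatment, and 6-month retention is one of the listed measures of individual-level Maintenance. An overstated figure would flatter the programme on that aim. The profile of defaulters and of deaths would also omit the earliest losses, who may differ from patients lost later. Section 3.4.5 compares patients by period of entry; if the single-visit share differs between periods, that comparison is affected for retention as well.

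**Working it through.** The protocol states no retention, default or death rate for the cohort, so there is no figure to reproduce. The check has two parts.

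**1. Does the rule exclude the events being measured?**

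Under the default definition used until October 2016 (section 3.4.2), a patient qualifies after 90 days without attending, if not known to have died or moved and not reached by phone on two occasions. The later definition replaces the 90 days with two consecutive missed appointments. Neither needs a second attended visit, but cohort entry does. A patient can therefore meet the default definition, or die, without ever becoming eligible for the cohort.

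**2. How large is the effect?**

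Let

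- s = share of enrolled patients with one visit only (not in the documents; assumed)
- r = 6-month retention among patients with at least two visits (assumed 90%)
- d = default among patients with at least two visits (assumed 10%)
- f = share of single-visit patients who count as defaulters (assumed 0.5 to 1)

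*Retention.* Among patients with 6 months of possible follow-up, a single-visit patient is taken as not active at 6 months. Then

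retention in all enrolled = r(1 - s), so the restricted figure is too high by the factor 1/(1 - s).

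| s | 0.90 × (1 - s) |
| --- | --- |
| 2% | 88.2% |
| 5% | 85.5% |
| 10% | 81.0% |

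*Default, if the two-visit rule also governs the active cohort.*

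default in all enrolled = d(1 - s) + s·f

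| s | f = 0.5 | f = 1 |
| --- | --- | --- |
| 2% | 0.098 + 0.010 = 10.8% | 0.098 + 0.020 = 11.8% |
| 5% | 0.095 + 0.025 = 12.0% | 0.095 + 0.050 = 14.5% |
| 10% | 0.090 + 0.050 = 14.0% | 0.090 + 0.100 = 19.0% |

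The understatement is s(f - d). It is positive only when f exceeds d, that is, when single-visit patients default more often than those who return.

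*Scale.* With n = 3500 (an assumption, taken from the enrolment count of over 3500 in section 1.1.1), the 95% confidence half-width for a proportion of 10% or 90% is 1.96 × √(0.1 × 0.9 / 3500) = 0.0099, about 1.0 percentage point. The retention bias is r·s = 0.9s, which passes that half-width once s exceeds 0.0099 / 0.9 = 1.1%.

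*Deaths.* Table 2 asks only for a description of those who died. No rate is defined, so there is no arithmetic to do; early deaths are simply absent from the description.

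**The case against.** The strongest reply is that the link to default is an inference. Table 2 sets defaulters against the active cohort, while the two-visit rule is stated for the study cohort. The programme also records exits as operational data (section 1.1.6) and counts them monthly (Table 1), with no visit condition. The protocol never says that the active cohort carries the rule. This stands: the default bias is conditional. It does not rescue 6-month retention, where no other denominator is offered. Default is also reported as a trend, and a steady single-visit share would shift its level more than its direction.

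Four stronger readings are tempting, and the documents do not support them.

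- *Section 3.3 flatly contradicts 3.4.1.* Section 3.3 gives the general population and refers eligibility to the method sub-sections, so 3.4.1 governs and the executive summary agrees with it. The wording of 3.3 is loose and should be aligned. If 3.3 were what is meant, the bias would not arise.
- *Mortality is understated.* No death rate is defined, so none is biased.
- *The single-visit share is about 25%.* Section 3.3 counts 4672 registrations and section 1.1.1 over 3500 enrolments, both for November 2016. The first covers NCD-related registrations aged 1 to 94, and section 1.1.2 has suspected cases directed to the service too. Nothing ties the gap to single visits.
- *All single-visit patients are defaulters.* That is the extreme case, f = 1. The definition leaves out patients known to have died or moved, or reached by phone, and recent enrolees may not yet be due back.

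It is also fair to say that the study is descriptive, has no comparator and states its visit rule openly. That limits the harm but does not make the retention figure right.

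**Conclusion.** The point holds for 6-month retention. As written, the rule overstates it by 1/(1 - s), and the direction does not depend on any assumed rate, only on single-visit patients not being active at 6 months. For default the understatement is conditional: the rule must apply to the active cohort, and single-visit patients must default more often than the rest. For deaths and for the profile of defaulters, the earliest cases are missing.

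The size cannot be fixed from the documents because s is not given. On the illustrative assumptions above, with s = 5%, reported retention of 90% would be 85.5% among all enrolled patients, and reported default of 10% would be 12.0% to 14.5%. Using at least two visits for change-from-baseline and last-value clinical outcomes is sound and is not in dispute.

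**What to change.** Define two analysis sets in section 3.4.1.

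- **Two-visit set:** as now, for change-from-baseline and last-value clinical outcomes.
- **All eligible enrolled patients aged six or older, from the first visit:** for 6-month retention, for default and for the description of deaths. Limit retention to patients whose enrolment date allows 6 months of observation before the records cut-off, and default to those with enough time to meet the default definition.

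State in Table 2 which set the active cohort refers to. Report the number and characteristics of single-visit patients. Align section 3.3 and the executive summary with 3.4.1.

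Leave the denominators of the process indicators as they are. Many are annual checks that a patient seen once had little chance to receive, and no fault in them has been shown.

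The cost is protocol wording and one further denominator from records the programme already holds. The reported retention and default figures will look somewhat less favourable.

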### 3.4.2 Cohort study main outcome measures

The principal **clinical outcome measures** for patients in the cohort are:

DM: HbA1c < 7 or 8%; proportion of patients meeting individualised target at last visit within the reporting period and trend from baseline

Hypertension: BP < 140/90 mmHg: proportion of patients at target at last visit within the reporting period and trend from baseline

Cardiovascular disease: change in total cholesterol level from baseline

Asthma / COPD: Free from exacerbations / admissions in last six months

The principal **quality of care outcome measures** are the following:

Number/ % of active patients with CVD prescribed a statin during reporting period

Number/ % of patients with CVD prescribed aspirin during reporting period

Number/ % of patients with CVD prescribed at least one anti-hypertensive during reporting period

Number/% of patients with COPD/asthma with inhaler technique check documented

Number/ % of times when appropriate clinical action taken based on clinical or laboratory findings according to guideline (see Annexe 2e for detail)

Description of trends and patient characteristics in programme defaulters and deaths

Proportion of recommended referrals to other services that are appropriate as per guideline

Death is defined as confirmed death reported by family or community member. A defaulter is defined as a patient who has not attended any NCD clinic appointments within the last 90 days, is not known to have died or moved out of the area, and has not been successfully contacted by phone on two occasions by the clinic registrar. The definition was changed in October 2016 to reflect the newly extended appointment interval for stable patients to: two consecutive missed appointments; not known to have died, moved out of the area, or become immobile and ineligible for home care; and has not been successfully contacted by phone on two occasions by the clinic registrar.

Exacerbation of respiratory condition refers to self-reported or documented temporary, usually reversible, worsening of the condition requiring a step-up in treatment or hospitalisation, depending on severity. Acute referral to specialist care or to the emergency room is recommended by the NCD guideline when the condition is not controlled by the maximum available primary-level treatment; additional secondary-care level diagnostics or treatments are required; in an uncontrolled acute exacerbation; or in cases of clinical uncertainty. Specific referral criteria for each condition are further described in the guideline.

Other outcome measures are listed in Table 2 (page 26).

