Health promoters provide individually tailored health education at each clinical contact. Topics covered include: education about diagnosis and disease, treatment and adherence support, patient concerns and expectations, and lifestyle changes. Motivational interviewing techniques are used to support patients to make lifestyle modifications related to diet, exercise levels and smoking. On enrolment, the doctor and health educator see patients for thirty minutes each; patients on return visits spend approximately fifteen minutes each with clinical staff (either a doctor or nurse) and a health educator.

Routine laboratory tests are carried out at a local laboratory, which has been quality assured by MSF. At the first visit a urine dipstick (for white cells, red cells and protein) is performed. A routine set of blood tests is carried out: haemoglobin (Hb), kidney function tests (sodium, potassium, creatinine), fasting blood glucose, liver function tests (LFTs), cholesterol profile (total cholesterol and triglycerides), glycosylated haemoglobin (HbA1c) and microalbuminuria for known diabetics, and thyroid function tests (free thyroxine and thyroid stimulating hormone) for patients with known thyroid disease. Fasting plasma glucose and HbA1c are repeated at 3-monthly intervals for diabetic patients; urine dipstick is repeated biannually; and cholesterol profile, kidney function tests and microalbuminuria are repeated annually. The other named tests are repeated as required according to clinical protocols.

Medications are those that are considered standard of care in Jordan; most are on the MSF Green List, the list of medications approved for use in MSF projects, with some additions relevant to the local context. Medications are dispensed from the MSF pharmacy, located onsite at each clinic immediately following a medical consultation. Prescriptions are renewed at maximum one-monthly intervals. Patient data are maintained in paper-based purpose-designed chronic care files, which are stored securely at each clinic.

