### 1.1.6 Existing data sources, records and assessment processes

Routine cohort data are recorded in a paper-based patient file and entered daily into a purpose-designed MS Excel database by a trained data entry operator. The demographic data collected include: age, gender, mobile phone number, highest level of education; country of origin; refugee status and governorate of origin if Syrian; and insurance status if Jordanian. Data on Syrian refugees’ date of arrival in Jordan, UNHCR registration and Ministry of Interior card status are also collected if appropriate. Socio-demographic data are recorded on household size and crowdedness, type of dwelling and household makeup including gender and highest level of education attained by household head. Factors affecting treatment access and adherence are also documented i.e. impaired mobility and whether living with a treatment supporter.

Clinical data collected at the patient’s first visit include medical history, family history of relevant NCDs, lifestyle factors (smoking, alcohol consumption and exercise levels) and baseline vital signs (BMI, waist circumference, blood pressure, heart rate, blood sugar level and cardiovascular risk score assessment). New diagnoses; numbers, types, doses and reason to adapt medications; recommended specialist referral; and referral for laboratory tests are recorded at the first and each subsequent clinical visit.

At review visits, nurses record repeat vital signs and laboratory results; health educators record current exercise levels, smoking status and current stage of change on the Prochaska and DiClemente stages of change model for behaviour change. Symptom and functionality scores are recorded before and after a course of individual counselling, using Generalized Anxiety Disorder 7-item Scale (GAD7), Patient Health Questionnaire for Depression (PHQ 9) and a locally devised four-item screening tool for PTSD. These tools will be revised in early 2017.

Operational data recorded include numbers of new and follow-up medical consultations per month, type of consultation (nurse, doctor, home visit team), number of referrals made, number of health education sessions attended and programme exits (death, defaulter, voluntary defaulter). The number of MHPSS discussion groups, psycho-education sessions and individual counselling sessions undertaken per month are also recorded.

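### The three parallel CVD prescribing measures use different denominators: active patients for the statin, all patients with CVD for aspirin and anti-hypertensives

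*Protocol*

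**What the plan says.** Protocol section 3.4.2 names these among its principal quality of care measures, one after another:

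- Statin: "Number/ % of active patients with CVD prescribed a statin during reporting period"
- Aspirin: "Number/ % of patients with CVD prescribed aspirin during reporting period"
- Anti-hypertensive: "Number/ % of patients with CVD prescribed at least one anti-hypertensive during reporting period"

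The quality indicator rows of Table 2 carry the same three lines with the same difference.

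Section 3.4.1 admits to the study cohort all NCD patients aged six or over with at least two recorded visits; it does not require them to be still in care. Section 1.1.6 records exits as death, default and voluntary default, and section 3.4.2 makes defaulters and deaths an outcome.

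On timing, section 3.4.2 judges blood pressure as the "proportion of patients at target at last visit within the reporting period and trend from baseline" and uses a last-visit basis for HbA1c too. Table 2, under Maintenance, takes "Numbers of medications and daily pill count at last consultation during reported period". Section 1.1.6 says that "numbers, types, doses and reason to adapt medications" are recorded at the first and each later visit, and section 1.1.2 says: "Prescriptions are renewed at maximum one-monthly intervals".

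**The concern.** Section 3.4 says the cohort study will assess how consistently the programme applies guideline interventions, and gives statin prescribing as its example. A reader will naturally set the three CVD percentages next to one another. If patients who left are excluded from one and kept in the other two, part of any difference between drugs reflects who was counted, not what was prescribed. The same difference stands in both places where an analyst would look for the definition, so following the protocol faithfully would reproduce it.

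The word *active* carries a further risk. If it depends on defaulter status, section 3.4.2 reports that the defaulter definition changed in October 2016, inside the January 2015 to December 2016 record window of section 3.4.3. That change would move the statin denominator and leave the other two untouched.

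A secondary point is the time basis. The prescribing measures ask whether a drug was prescribed in the period, while the control and pill-count indicators ask about the last visit. The two sets therefore do not describe the same moment.

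**Working it through.** The protocol states no expected rate, sample size or test for these measures, so there is no figure to reproduce. The check is first of the text and then of the possible size.

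**Text, section 3.4.2 and Table 2**

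| Measure | Denominator | Numerator timing |
| --- | --- | --- |
| Statin | active patients with CVD | any time in the period |
| Aspirin | patients with CVD | any time in the period |
| Anti-hypertensive | patients with CVD | any time in the period |
| Blood pressure, HbA1c | (disease group) | last visit in the period |
| Pill count (Table 2) | (not stated) | last consultation in the period |

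The restriction to active patients appears in one of three denominators, in both places. The numerator is the same for all three drugs. Since the cohort keeps people who exit, the two denominators hold different people as soon as anyone with CVD has left.

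**Size of the denominator effect (all inputs assumed)**

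Let L be the share of CVD patients who left, p the share of stayers prescribed the drug in the period, and q the same share among leavers.

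- Active-only denominator: rate = p.
- All-patient denominator: rate = (1 − L) × p + L × q.
- Gap = L × (p − q).

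With p = 80%:

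| L | q = 80% | q = 60% | q = 40% |
| --- | --- | --- | --- |
| 10% | 0 points | 0.10 × 20 = 2 | 0.10 × 40 = 4 |
| 20% | 0 points | 0.20 × 20 = 4 | 0.20 × 40 = 8 |
| 30% | 0 points | 0.30 × 20 = 6 | 0.30 × 40 = 12 |

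Two drugs prescribed identically would thus be reported as 80% for the statin and 68 to 80% for aspirin.

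**What a last-consultation figure would add (all inputs assumed)**

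If a share E is prescribed the drug at some time in the period and a share s of those have it stopped before the last consultation, the share with it on the last prescription is E × (1 − s). With E = 80%:

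- s = 5%: 0.80 × 0.95 = 76%, 4 points lower.
- s = 10%: 0.80 × 0.90 = 72%, 8 points lower.
- s = 20%: 0.80 × 0.80 = 64%, 16 points lower.

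These differences are not errors in the stated measure. They show what it leaves unseen when the period is long enough for a drug to be started and stopped within it.

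**The case against.** The strongest reply is that one word differs across three descriptive lines and no planned inference depends on it. Section 3.4.5 plans proportions with confidence intervals, comparison by period of entry, and regression of clinical outcomes; it does not plan to compare statin with aspirin. Guideline implementation is also judged by the clinical audit and by the other quality measures. All of this stands, and it limits the consequence to percentages that cannot be read side by side; no error rate is affected.

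It can also be said that the meanings of *active* and *reporting period* belong in a statistical analysis plan. Leaving those terms for later is fair. The mismatch is different: the protocol states it, twice.

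A reader might go further and infer that stopped drugs always score as successes, so that discontinuation can never lower any of the three measures. The documents do not support that. Prescriptions are renewed at least monthly, so with any period shorter than the whole record a drug stopped before the period began is not counted. The protocol does not fix the period at 24 months, and most of the quality indicators in Table 1 look back one year. Prescribed in the period is a coherent process measure; replacing it outright with last-visit status would be partly a preference, and would score a drug stopped for a documented reason as not prescribed.

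A reader might also infer a denominator gap of 16 points (80% against 0.80 × 0.80 = 64%). That needs 20% to have left before the period started and still to be counted in it with no visit and no prescription. The protocol does not say that patients absent from a period are counted in it.

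**Conclusion.** The point holds for the denominators. Three parallel principal measures follow different stated rules, in section 3.4.2 and again in Table 2, and their percentages are not comparable as written. The size cannot be computed from the documents. Under the assumed range above it is 0 to 12 points, and it is zero if leavers were prescribed the drug at the same rate within the period.

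The numerator is usable as it stands. The lesser observation is that prescribing is reported on a different time basis from blood pressure, HbA1c and pill count, although the visit-level records would allow both.

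This concerns measurement only and says nothing about which patients should receive a drug.

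**What to change.** In section 3.4.2 and in Table 2, use one denominator for the statin, aspirin and anti-hypertensive measures, for example patients with CVD who had at least one medical consultation in the reporting period. Patients with no consultation in the period then drop out of all three alike, and the defaulter and death measures still describe those who left the programme.

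Keep prescribed during the reporting period as the numerator. Add for each drug the proportion with it on the prescription at the last consultation in that period, so that prescribing can be read on the same time basis as the control and pill-count indicators.

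The cost is a wording change in two places and slightly more tabulation. The medication data are already recorded at every visit. The reported percentages may change modestly.
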